#### Secondary outcome measures

Single assessment numeric evaluation (SANE): Single assessment numeric evaluation questions have been used previously in participants with neck pain [38], shoulder surgery [39] and anterior cruciate ligament reconstruction [40] and been shown to correlate well with other outcome measures. Participants will be asked:(i)“How would you rate your knee today as a percentage of normal on a scale of 0% to 100%?” with 100% being defined as having no problems at all with the knee. (at 0, 6 and 12 weeks)(ii)“On a scale of 0 (not at all) to 100% (totally recovered), how well do you feel you have recovered from your knee pain?” (at 6 and 12 weeks)

Patient acceptable symptom state (6 and 12 weeks): Patient acceptable symptom state is defined as the highest level of symptom beyond which patients consider themselves well [41]. Patient acceptable symptom state has been used in musculoskeletal and rheumatic conditions and shown to provide information about a patient’s improvement exceeding the minimally clinically important improvement [41–43]. Participants will be asked to answer yes or no to a structured question: “Is your current condition satisfactory, when you take your general functioning and your current pain into consideration?”

Perception of success and willingness to recommend the treatment (6 and 12 weeks): Participants will be asked to answer yes or no to two questions in regards to their perception of the success of their treatment:(i)“Overall, would you agree that the treatment you have received has been successful for your knee pain?”(ii)“If a good friend has the same knee pain as you, would you recommend the same treatment you received?”

Patient satisfaction (6 and 12 weeks): Participants will be asked two questions in regards to the satisfaction of their treatment with a selection of five possible responses (very satisfied, somewhat satisfied, neither satisfied not dissatisfied, somewhat dissatisfied, very dissatisfied). The questions will be:(i)“Over the course of treatment for your knee pain, how satisfied were you with your overall treatment?”(ii)“If you had to live with the symptoms you have right now, how would you feel about it?”

Numerical pain rating scale (0, 6 and 12 weeks): The numerical pain rating scale (NPS) can be a verbal or visual scale to grade the intensity of pain experienced by the participant and is recommended for research purposes [44]. Participants will be asked to indicate a score that best represents the intensity of their knee pain on an 11-point scale where 0 represents no pain and 10 represents worst pain imaginable. Participants will provide two ratings; their average pain over the previous seven days and their worst pain over the previous seven days. An improvement of ≥ 2 on the NPS indicates clinically meaningful change [45, 46].

Patient specific functional scale (0, 6 and 12 weeks): Participants will self-select up to five tasks or activities that are impaired due to their symptoms. Participants will then rate the level of impairment of each task/activity on an 11-point scale from 0 (“unable to perform activity”) to 10 (“able to perform activity at same level as before the injury or problem”). The patient specific functional scale is a reliable and valid tool that is sensitive to changes in patient’s symptoms [47, 48]. It has been reported that a change of three or more on an individual patient-nominated activity indicates a true change in functional capacity [48].

Kujala Patellofemoral Scale (0, 6 and 12 weeks): This questionnaire comprises 13 items designed specifically for PFP. Categories within the questionnaire cover a range of knee functions under varying loads. Participants select a response to each of the 13 items that best depicts their symptoms. Each item is weighted separately and then summed overall, with the highest possible score of 100 points representing pain free full function and 0 representing total incapacity. This questionnaire has been recommended for knee pain because it is reliable and sensitive to changes in symptoms [49–51]. A change of 10 points is considered as the minimum clinically important difference [50] in patients with PFP.

Knee injury and osteoarthritis outcome scale (KOOS) (0, 6 and 12 weeks): This questionnaire is comprised of five separate subscales that assess the patient’s opinion of their knee and symptoms. The subscales cover pain, symptoms, activities of daily living function, sporting and recreation function and quality of life. Each subscale consists of standardized answers (five Likert boxes), with each question scored 0–4 separately. The questionnaire will be scored according to the 2012 KOOS scoring manual. Participants select a response to each question in each subscale that best depicts their symptoms. Each subscale will be normalised to a scale of 0–100 (0 = extreme problems, 100 = no problems). A change of 8–10 points is suggested to represent a clinically significant change in symptoms [52].

Hospital anxiety and depression scale (HADS) (0, 6 and 12 weeks): This 14-item scale will be used to investigate emotional states of those with PFP. It has been found to be a reliable instrument for detection of anxiety and depression in an outpatient setting and a valid indicator of severity [53, 54]. Participants are required to select the best of four responses to questions pertaining to either anxiety or depression (seven questions each), which are scored from 0 to 3. The scores for the anxiety and depression questions are summed separately to give total scores for each component, where 0–7 represents no anxiety or depression, 8–10 is borderline, and 11–21 indicates the presence of an anxious or depressive state.

Euro-Qol™ (EQ-5D 3 L version) (0, 6 and 12 weeks): This validated questionnaire is used as a measure of health outcome and provides a simple descriptive profile and a single index value for health status. It compromises of five domains about mobility, usual activities, self care, pain and discomfort, and anxiety or depression [55]. Participants will be asked to rate their impairment on each domain (none, moderate or severe problems). Each health state is scored (1–3) and transformed into an index score. This score is used to derive quality-adjusted life years as an outcome measure and is one of the most commonly used economic evaluations used to inform decisions in health care [56]. The participant scores their overall health on a 0 to 100 scale, where 100 represents complete health and well-being [55].

Tampa scale for kinesophobia (TSK) (0, 6 and 12 weeks): The TSK is a 17-item questionnaire aimed at assessing fear of reinjury due to physical movement [57]. Each item is scored on a 4-point Likert scale that ranges from strongly disagree (1) to strongly agree (4). The inverse scores from items 4, 8, 12, and 16 are used to calculate the total score. Total TSK scores range between 17 and 68, with higher scores suggestive of higher levels of fear of physical movement and vulnerability.

Pain Catastrophising Scale (PCS) (0, 6 and 12 weeks): The PCS is a 13-item valid and reliable questionnaire that evaluates a participant’s level of pain catastrophic thinking, and classifying this into levels of rumination, magnification and helplessness [58]. Participants are asked to reflect on past painful experiences, and to indicate the degree to which they experienced certain thoughts or feelings when experiencing pain, on 5-point scales from not at all (0) to all the time (4). The PCS yields a total score and three subscale scores for rumination, magnification and helplessness respectively. The total score ranges from 0 – 52, with higher scores indicating higher levels of pain catastrophization.

Functional tests: Step down, step up and squat (0, 6 and 12 weeks): These functional tests are commonly reported as aggravating activities by patients with PFP because they load the patellofemoral joint and have been previously used in clinical trials [10]. Repeated step testing will be performed on a single 25 cm step in time with a metronome set at 96 beats per minute (e.g., stepping up/down on each beat). Repeated squats will be performed in time with a metronome set to 96 beats per minutes feet shoulder width apart, squatting down in two beats, until the participant can touch both lateral malleoli with their fingers, and standing up over two beats. Activities will be stopped when either a) onset of symptoms occurs, or b) there is an increase in existing symptoms or c) when a maximum of 25 repetitions has been reached without the onset of pain.

### Physical measurements

An examiner at each trial site, who is blinded to treatment allocation and midfoot width mobility stratification, will collect self-reported questionnaires (i.e., pain scores, Kujala Patellofemoral Scale, etc.), physical measurements and demographic data prior to commencement of the intervention and at follow-up. Physical measurements will include foot posture measurements, ankle, hip and first metatarsophalangeal range of motion measurements and maximal isometric hip strength testing. These measures will be used in post-hoc analyses of prognostication and identification of other possible candidates for treatment effect modifiers.

Midfoot width and height mobility: Measurement of the width and height at the midfoot (i.e. 50% of total foot length) has been previously described and demonstrated to be reliable [17]. In brief, these measurements are performed on a foot measurement platform that can standardize foot position by placing heels 15.24 cm apart with the first metatarsal heads against a guide with body weight equally distributed on both feet. Midfoot width in weight bearing is measured using a digital caliper with extend arms, which are positioned perpendicular to the sole of foot and adjacent to lateral and medial aspect of the foot at the 50% length (Fig. 8). This is repeated in non-weight bearing with the patient seated on a height adjustable table and legs hanging freely (Fig. 9). Midfoot height (dorsal arch height) measurements at 50% of the total foot length in weight bearing (bipedal stance) and minimal weight bearing postures will also be taken (Fig. 10) [17]. To measure the arch height in a minimal weight bearing posture, the participant sits on a height adjustable plinth with their feet hanging freely. The assessment platform is positioned under both feet and the plinth is lowered until the point of the heel being assessed just contacts the platform. The vertical height of the arch is then measured. The height and width measurements of each foot in weight bearing and non (or minimal) weight bearing will be recorded separately three times and then averaged to give a single value for the analysis. The change in midfoot height and width is calculated by subtracting the measures in the two weight bearing conditions.

**Fig. 8 Fig8:**
[figure not shown]
Midfoot width measured in weight bearing

**Fig. 9 Fig9:**
[figure not shown]
Midfoot width measured in non-weight bearing

**Fig. 10 Fig10:**
[figure not shown]
Midfoot arch height measurement

Navicular drop: The participant stands barefoot with equal weight on both feet. The navicular tuberosity will be identified using palpation and the most prominent point marked using a water-soluble ink pen. With the patient standing in subtalar joint neutral position (defined by palpation of the talus in the mortise and scored ‘0’ on the foot posture index [59]), the height of the navicular tuberosity will be measured using a clear angle ruler. The participant is instructed to relax their feet and the navicular tuberosity height is re-measured. The difference in height measurements between a subtalar joint neutral and relaxed foot position will be calculated to determine the amount of navicular drop [60–63].

The Foot Posture Index (FPI-6): Relaxed foot posture will be assessed using the FPI-6, which consists of six criteria: (i) talar head palpation, (ii) curves above and below the lateral malleoli, (iii) inversion/eversion of the calcaneus, (iv) bulge in the region of the talonavicular joint, (v) congruence of the medial longitudinal arch and (vi) abduction/adduction of the forefoot on the rearfoot [59]. Each criterion is examined and scored on a 5-point scale between −2 and +2, which are then totaled to categorize the foot as being highly pronated, pronated, normal, supinated, or highly supinated [59]. Intrarater reliability has been reported to be very good with interrater reliability being only moderate between three raters [64, 65].

Weight bearing bent knee ankle dorsiflexion (Lunge Ankle Dorsiflexion Device - LAD): Bent knee ankle dorsiflexion will be measured using a bespoke device, the Lunge Ankle Dorsiflexion measurement device (LAD). The LAD device has been previously described [66]. In brief, the LAD was designed with only one degree of freedom of motion in the sagittal plane. The patient’s foot is aligned in a sagittal plane with a line that bisects the 2nd and 3rd phalanges and the midline of the posterior calcaneus. Whilst maintaining the toe in light contact with the front of the reference block, the participant slowly lunges forward, with the knee in contact with a mobile measurement indicator. The therapist focuses on ensuring that the three points remain in the sagittal plane by watching for heel drift (usually medially) and heel lift, which indicates that full dorsiflexion has been reached. The linear measurement of horizontal distance between anterior knee and the fixed reference block at the longest toe is read from a ruler (mm).

Hip strength: Strength of the hip abductors, adductors and external rotators will be measured at baseline, 6 and 12 weeks as dysfunction in these muscle groups has been identified as a common impairment within the PFP population, [67–69] and will be used in post hoc exploratory prognostic analyses. Force produced during a maximal voluntary isometric contraction (MVIC) will be measured with a hand held dynamometer (Nicholas, Lafayette, IN47903, USA) Measurements will take place in supine to minimize the effect of gravity during testing and compensatory contractions [70]. Each participant will complete two practice contractions (50% MVIC followed by 100% MVIC) followed by three experimental MVICs where the participant will be asked to contract maximally for 5 s. Participants will have a 30 s rest between each contraction. The peak force (Newtons) will be recorded for each contraction and converted to torque (using the distance between the point or rotation and placement of dynamometer as the lever arm) standardized to body mass (Nm/kg). Hip abductor and hip adductor muscle strength will be tested using a dynamometer 5 cm proximal to the lateral and medial malleolus respectively, and stabilised by a rigid belt. The test leg will be extended in 0° abduction and 0° flexion, with the non-test hip and knee flexed (Fig. 11). Hip external rotation will be measured in supine with the hips in 30° of flexion with the dynamometer 5 cm proximal to the medial malleolus, stabilised in a solid bracket, fixated to the testing device (Fig. 12). This testing position was chosen because it: corresponds to biomechanical data on muscular actions of the external rotators in various degrees of hip flexion (i.e., piriformis being an external rotator muscle at 0° flexion and functionally switch rotation action to internal rotation at >60° hip flexion); [71, 72] replicates the position of exercise in the hip intervention protocol [27]; and approximates the degrees of hip flexion relative to the pelvis during foot contact/limb loading in the initial stance phase of gait [73–75].

**Fig. 11 Fig11:**
[figure not shown]
Hip abduction strength testing

**Fig. 12 Fig12:**
[figure not shown]
Hip external rotation strength testing in 30° hip flexion

Limb length for the hip abductor and adductor measurements, will be measured from the participant’s anterior superior iliac spine to a mark 5 cm proximal from the lateral and medial malleolus, respectively. For hip external rotation, distance will be measured from the medial joint line to a mark 5 cm proximal to the medial malleoli. Participants will be instructed to hold the sides of the plinth for stabilization and receive a standard verbal encouragement with consistent level of volume and enthusiasm.

Hip range of motion: Passive hip internal and external rotation range of motion will be measured in upright sitting, arms crossed, knees flexed to 90° over the edge of the plinth and the non-test leg stabilised by a rigid belt. The hip will be passively rotated to the point of resistance with no compensatory pelvic motion. Range will be measured using a plurimeter placed 5 cm proximal to the tip of the tibial malleoli on the medial border of the tibia for external rotation, and 5 cm proximal to the tip of the lateral malleoli to measure internal rotation (Fig. 13).

**Fig. 13 Fig13:**
[figure not shown]
Hip internal and external range of motion measuring

Demographic and other information: Other baseline measurements to be collected will include age, sex, height, weight, body mass index (BMI), unilateral and bilateral symptoms, duration of symptoms, use of medications, physical activity levels, joint mobility using the Beighton and Horan Joint Mobility Index [59, 64] and reported crepitus during daily living activities.

### Participant timeline

Volunteers will be recruited into the study through a structured process involving a comprehensive advertising campaign followed by verbal and physical examination screening of eligibility by a registered physiotherapist. Participants who meet the eligibility criteria will be offered enrolment into the study, complete consent forms then undergo baseline measurements and randomly allocated to an intervention (Fig. 14). Participants with bilateral symptoms will nominate their most symptomatic knee to be used in analysis. The timeline for events (e.g., outcome measure timepoints and close out) are shown in Table 3.

**Fig. 14 Fig14:**
[figure not shown]
Flowchart of participants through trial (consort)

**Table 3 Tab3:** SPIRIT figure. Schedule of enrolment, interventions and assessments

		Trial period								
	Enrolment	Allocation	Intervention period						Follow up	Close out
	May 2014– November 2016	May 2014– November 2016	Week 1	Week 2	Week 3	Week 4	Week 5	Week 6	Week 6	August 2014 – Feb 2017
Enrolment										
Eligibility screening	X									
Informed Consent	X									
Allocation		X								
Intervention										
Foot orthoses			X	X	X	X	X	X		
Hip exercises			X	X	X	X				
Assessment										
Diagnosis	X									
Midfoot width mobility	X									
Demographics		X								
Global rating of change									X	X
Rate of recovery									X	X
Patient acceptable symptom state									X	X
Numerical pain rating		X							X	X
PSFS		X							X	X
Kujala		X							X	X
KOOS		X							X	X
HADS		X							X	X
Euro-QoL		X							X	X
TSK		X							X	X
PCS		X							X	X
Functional tests: step up, step down, squat		X							X	X
Navicular height		X								X
Midfoot height mobility		X								X
Isometric hip strength testing		X							X	X
Range of motion measures		X							X	X

*Kujala* Kujala patellofemoral pain scale, *PSFS* patient specific functional scale, *KOOS* knee injury and osteoarthritis outcome scale, *HADS* hospital anxiety and depression scale, *TSK* Tampa scale for kinesophobia, *PCS* pain catastrophising scale

### Sample size

Sample size was based on proportions of patients rating themselves as “better” or “much better” on the Global Rating of Change (GROC) score in the foot orthoses and hip exercise treatment groups. The primary aim of the study is to determine whether midfoot width mobility is a treatment effect modifier for foot orthoses when compared to progressive resisted hip exercises. This requires testing for an interaction between midfoot width mobility, dichotomised as high (≥11 mm) or low (<11 mm), and treatment group. Based on previous findings, which indicated a strong effect of foot orthoses in patients with PFP who had a midfoot mobility ≥11 mm, [11] we wanted to be able to detect an interaction effect of 50 percentage points. This means that the difference between the foot orthoses and hip exercise groups in the proportions of participants who are improved at 12 weeks will be 50 percentage points higher (favoring foot orthoses) in participants with high midfoot width mobility than in those with low midfoot width mobility. A sample of 30 participants (15 per group) who have high midfoot width mobility provides 80% power using a two-sided significance level of 0.05 to detect a difference between the proportions of participants with improvement of 30% in the hip exercises group compared to 80% in the foot orthoses group. Assuming that 20% of participants will be in the high midfoot width mobility group, we inflated the sample size to 188 participants (94 per group) to ensure adequate power to detect this interaction effect of 50 percentage points [76]. To allow loss to follow-up of up to 15%, the final sample size was 220 participants (110 per group).

### Recruitment

A comprehensive recruitment strategy, successfully utilized in previous clinical trials [11, 18] will be used in regions of Brisbane, Australia and Aalborg, Denmark. The recruitment strategy involves paid advertisements in local and regional newspapers, supplemented by advertisements on university, gymnasium and community websites, online social media, electronic and paper noticeboards within the catchment area at regular intervals during the recruitment period. Further referrals may come from physiotherapists involved in the study and general practitioners, through the provision of information and advertising packages at their practices. Volunteers who express interest in participating will be screened through the previously described two-stage screening process to determine eligibility.

### Allocation

Once informed consent and baseline measurements have been obtained, each participant will be randomly allocated to one of two intervention groups via concealed allocation and assigned a participant code. An independent off-site body will generate a randomization schedule for all participants at both the Australian and Danish sites. The randomization schedule will be generated by computer and allocate on a 1:1 basis to each of the treatments with stratification on the midfoot width mobility measure.

### Statistical methods

A biostatistician who is blind to treatment group allocation and midfoot width mobility will conduct analysis. All participants who have missing data and did not fully comply with the treatment protocol will be included in analyses. Demographic characteristics will be inspected to assess baseline comparability of treatment groups and compare those participants who remain in the study and those who withdraw. If the proportion of missing data for endpoints exceeds 5%, multiple imputation methodology will be applied. To test the hypothesis of interaction between randomised group and foot mobility, terms for randomised group and foot mobility group, together with an interaction between the two, will be included in models. For the primary outcome (dichotomised GROC) and other binary secondary outcomes, binary regression models with a logarithmic link will be fit. For other outcomes, linear regression models will be fitted, and assumptions will be assessed using standard diagnostic plots. To test for an overall treatment effect, regression models for outcomes will include terms for randomised group and foot mobility (as foot mobility is a stratifying variable).

We will also undertake a secondary analysis to further explore the relationship between midfoot width mobility and the outcome, whereby midfoot width mobility will be included in the model as a continuous variable, together with an interaction term with randomised group. Relationships will be investigated using fractional polynomials [77]. We elected to perform this secondary analysis because previous studies that identified midfoot width mobility as a potential predictor of outcome after foot orthoses used data-dependent techniques in relatively small samples to establish a cut-off value for “high” midfoot width mobility. The concern with establishing cut-off values with data-dependent techniques is that, while the cut-off value may have been “optimal” for the original sample, this same cut-off value may not be optimal in the larger population [78, 79].

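### The stated primary GROC models use no baseline severity covariate, which gives up some precision in an interaction that rests on about 19 high-mobility participants per arm

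*Protocol article*

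**What the plan says.** The Statistical methods section of the protocol article sets out two models for the dichotomised global rating of change (GROC). For effect modification, "terms for randomised group and foot mobility group, together with an interaction between the two, will be included in models". For the overall treatment effect, the terms are randomised group and foot mobility, and mobility is included because it is a stratification factor. Both are binary regressions with a log link. On baseline data, the same section says that "Demographic characteristics will be inspected to assess baseline comparability of treatment groups".

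The Sample size section makes the interaction the primary aim: "we wanted to be able to detect an interaction effect of 50 percentage points". Its starting point is the high-mobility stratum: "A sample of 30 participants (15 per group) who have high midfoot width mobility provides 80% power using a two-sided significance level of 0.05", for "improvement of 30% in the hip exercises group compared to 80% in the foot orthoses group". The total then follows from a prevalence: "Assuming that 20% of participants will be in the high midfoot width mobility group".

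Severity and chronicity are measured before treatment. Under Secondary outcome measures, the numerical pain rating is taken at weeks 0, 6 and 12 and covers "their average pain over the previous seven days and their worst pain over the previous seven days". The baseline items under Demographic and other information include "unilateral and bilateral symptoms, duration of symptoms".

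**The concern.** GROC is a rating of change and has no baseline value of its own. Severity at entry can therefore come into the primary analysis only as a named covariate, and none is named. If pain intensity or duration at entry predicts who reports success, that predictable part of the outcome stays in the residual variation of the interaction estimate. The interaction is the least precise quantity in the trial, because most of its variance comes from one small stratum. At stake is some avoidable width in its confidence interval, for data that the trial already collects. Covariates are credible only if they are fixed before unblinding, so the choice has to be made in advance.

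**Working it through.** **Inputs from the Sample size section.** Success 80% against 30% in the high-mobility stratum; two-sided 0.05; 80% power; 20% high mobility; 188 evaluable (94 per arm); 220 randomised.

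**Assumptions.** Low-mobility success of 30% in both arms, which makes the interaction 50 points. A covariate–outcome correlation of 0.2 to 0.5 on a latent normal scale. The document gives neither.

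**1. The plan's own figure.** With pooled variance, n = [1.96·√(2·0.55·0.45) + 0.8416·√(0.21 + 0.16)]² / 0.5² = (1.379 + 0.512)² / 0.25 = 14.3, so 15 per arm. This reproduces the stated number.

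**2. Size of the deciding stratum.** 0.20 × 94 = 18.8 evaluable per arm, about 19, with 75.2 low-mobility participants per arm. At randomisation it is 0.20 × 110 = 22 per arm.

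**3. Precision without covariates, risk-difference scale.** SE = √(0.37/18.8 + 2·0.3·0.7/75.2) = √(0.01968 + 0.00559) = 0.159. The high-mobility stratum supplies 0.01968/0.02527 = 78% of the variance. Power = Φ(0.50/0.159 − 1.96) = 0.88. Simulated trials with a robust test give about 0.85.

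**4. How much severity can vary by chance.** The SD of a standardised baseline difference is √(2/n): 0.33 at 18.8 per arm and 0.15 at 94 per arm. A difference of at least 0.5 SD has probability 12.5% in the high-mobility stratum and 0.06% between whole arms. With correlation ρ, such a difference moves the stratum's risk difference by Φ(q + 0.25ρ) − Φ(q − 0.25ρ), where q is the normal quantile of the success proportion. For ρ of 0.3 to 0.5 and success of 30% to 80%, that is 4 to 10 points, or about 0.25 to 0.6 of the 16-point SE.

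**5. Is this error or bias?** In simulated trials with no interaction (19 high and 75 low per arm), the mean estimate is about 0 with or without the covariate. The type I error is 0.057 unadjusted and 0.059 adjusted at a prognostic log-odds of 0.5 per SD, and 0.061 and 0.062 at 1.0. Adjustment removes no bias and corrects no error rate.

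**6. Gain from adjustment.**

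| Analysis simulated | Assumed prognostic strength | Effect of adjustment on the interaction |
|---|---|---|
| Linear-probability model, robust SE | correlation 0.2 / 0.3 / 0.4 / 0.5 | variance ratio 0.99 / 0.95 / 0.93 / 0.86 |
| Linear-probability model, robust SE | log-odds 0.5 / 1.0 per SD | SE 0.158 to 0.156 / 0.157 to 0.145; power 0.85 to 0.87 / 0.85 to 0.90 |
| Standardised logistic, one prognostic and one useless covariate | correlation 0.2 / 0.5 | variance lower by 1–2% / 12–16%; estimate unbiased; similar gains on the log-ratio scale |

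Putting the extremes into step 3: SE = 0.159·√0.99 = 0.158 gives power 0.885, and 0.159·√0.84 = 0.146 gives 0.93, against 0.882 unadjusted. By this formula the gain is under 1 point at the weak end and about 5 at the strong end. In evaluable participants it is worth 188/0.99 − 188 ≈ 2 to 188/0.84 − 188 ≈ 36.

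**The case against.** The strongest case against is that nothing here is an error. Treatment is randomised within the high-mobility stratum, so an unadjusted comparison is valid and its standard error already includes chance imbalance. That stands in full. A reader might infer from step 4 that imbalance biases the primary estimate or passes for effect modification; steps 3 and 5 show that it does not. In simulated trials selected for an imbalance above 0.5 SD, the unadjusted test does behave worse: false-positive rates are 0.07–0.11, against 0.05–0.07 adjusted. But that picks out unlucky allocations, and over all allocations the error rates are the same.

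A reader might also infer that comparability is checked only between whole arms and that a table of the four cells is needed. The article has one short sentence on the check and does not say only. Nor would inspecting the cells change the estimate.

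The size of the gain is open to challenge too. GROC asks participants to compare themselves with their own starting point, so a correlation of 0.3 to 0.5 with entry severity cannot be taken for granted; at 0.2 almost nothing is gained. Nor does the document show that worst pain and duration are the best two covariates. Both objections stand as limits on the benefit.

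Last, covariates are often left to the SAP, which is not shown. This stands in part. The article states the terms of both models and gives a reason for the one adjustment it makes, so the point contests a stated choice. If the SAP already names severity covariates, the point is met.

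**Conclusion.** The point holds as a modest, inexpensive gain in precision, and no more. The stated models for the primary outcome leave collected severity data unused while the main hypothesis depends on about 19 evaluable participants per arm in one stratum. The expected benefit is about 1% to 16% lower variance of the interaction, or roughly 1 to 5 points of power on the risk-difference scale. It rests on an assumed correlation of 0.2 to 0.5, on 20% high mobility, and on 80/30/30/30% success in the four cells. The document does not support a claim of bias, of inflated type I error, or of an invalid primary analysis.

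**What to change.** Before unblinding, name baseline worst pain over the previous seven days and symptom duration as covariates in both the GROC interaction model and the overall-effect model. Fit each as a logistic regression. For the interaction, average the predicted probabilities under each treatment over the participants of each mobility stratum; this gives the four standardised success proportions, from which the interaction is formed. A logistic fit is suggested because a log-link model with continuous covariates may not converge. Keep the unadjusted model as stated as a sensitivity analysis.

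The cost is a few lines of SAP text, two more parameters and one extra model, with no new data or participants. If the covariates prove weakly prognostic, the gain is negligible.
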